## Abstract

**Background:**

Claims made about the effects of treatments are very common in the media and in the population more generally. The ability of individuals to understand and assess such claims can affect their decisions and health outcomes. Many people in both low- and high-income countries have inadequate aptitude to assess information about the effects of treatments. As part of the Informed Healthcare Choices project, we have prepared a series of podcast episodes to help improve people’s ability to assess claims made about treatment effects. We will evaluate the effect of the Informed Healthcare Choices podcast on people’s ability to assess claims made about the benefits and harms of treatments. Our study population will be parents of primary school children in schools with limited educational and financial resources in Uganda.

**Methods:**

This will be a two-arm, parallel-group, individual-randomised trial. We will randomly allocate consenting participants who meet the inclusion criteria for the trial to either listen to nine episodes of the Informed Healthcare Choices podcast (intervention) or to listen to nine typical public service announcements about health issues (control). Each podcast includes a story about a treatment claim, a message about one key concept that we believe is important for people to be able to understand to assess treatment claims, an explanation of how that concept applies to the claim, and a second example illustrating the concept.

We designed the Claim Evaluation Tools to measure people’s ability to apply key concepts related to assessing claims made about the effects of treatments and making informed health care choices. The Claim Evaluation Tools that we will use include multiple-choice questions addressing each of the nine concepts covered by the podcast. Using the Claim Evaluation Tools, we will measure two primary outcomes: (1) the proportion that ‘pass’, based on an absolute standard and (2) the average score.

**Discussion:**

As far as we are aware this is the first randomised trial to assess the use of mass media to promote understanding of the key concepts needed to judge claims made about the effects of treatments.

**Trial registration:**

Pan African Clinical Trials Registry, PACTR201606001676150. Registered on 12 June 2016. http://www.pactr.org/ATMWeb/appmanager/atm/atmregistry?dar=true&tNo=PACTR201606001676150.

**Electronic supplementary material:**

The online version of this article (doi:10.1186/s13063-016-1745-y) contains supplementary material, which is available to authorized users.

## Background

The ability of individuals to obtain, process, and understand basic health information is a crucial element in making health care choices [1]. Such ability is often limited in both low- and high-income countries [2, 3]. Studies have revealed limited ability among patients, their caregivers and the public to assess the benefits and safety of treatments, and poor understanding of informed consent [4, 5], random allocation [6], risks [7, 8], and drug approval [9]. Some studies have found surprisingly low levels of knowledge of evidence-based medicine principles among health workers [10–12].

A poor understanding of health care evidence, and inadequate ability to recognise claims made about the effects of health care, can increase or diminish the willingness of individuals to seek care or participate in research. It may raise expectations (sometimes falsely), may dash hopes, or may provoke alarm (sometimes unnecessarily). It can result in low uptake of effective interventions, and inappropriate utilisation of health services [13]. It can also create communication barriers between health workers and patients [14, 15] and increase the costs of care [16, 17]. Despite these problems, there is only a handful of open-access tools to educate people to appraise information about the benefits and safety of treatments [18–22], or tools that simplify the interpretation of research information [23, 24]. To fill this gap, we have developed the Informed Healthcare Choices (IHC) resources which we are currently evaluating.

Improving access to reliable health information in the mass media – such as the Internet, radio, TV and print media – has the potential to affect individual health behaviours, health care utilisation, health care practices, and health policy [25, 26]. However, there are substantial barriers that prevent journalists from improving the scientific quality of their reports [27], and evaluations of health stories in the media have consistently found major shortcomings [28–30]. Therefore, users, listeners, viewers, and readers must be able to appraise the trustworthiness of claims in the mass media about the effects of treatments.

We have identified 32 key concepts that are relevant to evidence-informed decision-making that people need to understand and apply to assess the trustworthiness of claims made about treatment effects [31]. These concepts are grouped into six domains:Recognising the need for fair comparisons of treatmentsJudging whether a comparison of treatments is a fair comparisonUnderstanding the role of chanceConsidering all the relevant fair comparisonsUnderstanding the results of fair comparisons of treatmentsJudging whether fair comparisons of treatments are relevant

We have developed an educational podcast (a series of audio messages) to teach people how to apply nine of the 32 concepts in judging claims made about the effects of treatments. We settled for the nine concepts after a series of user-tests in which we identified some concepts as being more relevant than others for our target audience and easier than others for people to understand [32]. If resources allow, we plan to develop messages for other concepts, taking account of the lessons learned from this trial. The purpose of this randomised trial is, therefore, to evaluate the effects of this podcast on listeners’ abilities to assess claims made about the effectiveness and safety of treatments. We refer to this podcast as the Informed Healthcare Choices (IHC) podcast.

## Objectives

### Primary objective

To evaluate the effects of the IHC podcast on the ability of parents of primary school children to assess claims made about the effects of treatments.

### Secondary objectives

To evaluate the effects of the IHC podcast on listeners’ knowledge, attitudes, and intended behaviours regarding assessing claims and making decisionsTo compare participants’ self-assessed ability to assess the reliability of claims made about treatment effects and their objective ability as measured by the Claim Evaluation ToolsTo evaluate the effects of the IHC podcast 1-year post intervention

## Methods

### Study design

This will be a two-arm, parallel-group, individual-randomised trial evaluating the impacts of a podcast series designed to teach concepts of evidence-informed decision-making to parents of primary school children in Uganda (Fig. 1).

**Fig. 1 Fig1:**
[figure not shown]
Study flow chart

### Setting

The study will be conducted in central Uganda within the communities in which participants live and work. Uganda is a landlocked country in East-Central Africa. It is a multiethnic country with slightly over 70% of the population aged below 25 years. The country has a life expectancy at birth of 54.9 years, total fertility rate of 5.9 children, literacy rate of 78.4%, maternal mortality ratio of 343 per 100,000 live births, and infant mortality rate of 59 per 1000 live births. It has 0.1 physicians per 1000 people [33].

#### Study population and random allocation

Our study population will be parents of primary school children in schools with limited educational and financial resources. We will draw a sample of parents of children from schools participating in a cluster-randomised trial of IHC primary school resources, designed to help primary school children understand and assess claims made about treatment effects [34].

All public and private primary schools in the central region of Uganda will be eligible to participate in the IHC primary school resources trial. The only exclusions will be international schools, special needs children’s schools for the deaf and blind, and schools or classes that participated in the user-testing and piloting of the teaching resources. We intend to include at least 120 schools in that trial.

### Inclusion and exclusion criteria

#### Inclusion

Parents of children attending the schools participating in the trial of the IHC teaching resourcesThe ability to communicate in the language of the podcast (English or Luganda)Consent to participate in the study

#### Exclusion

Being unable to hearNot contactable by phoneHealth researchersParents who have participated in the development and user-testing of the podcastParents of children who participated in the development and user-testing of the children’s resources [34]

### Sampling technique

We will randomly select at least 30 schools among the 120 participating in the related trial evaluating the effectiveness of IHC materials designed for primary school children [34]. This number is informed by findings from our earlier engagements with parents, in which only about 10 to 20 parents attended meetings that are not on the usual school programme. About half of the schools selected will be from the intervention arm and the other half from the control arm of the schools participating in the trial evaluating primary school resources. In each of the selected schools we will create a list of parents of P.5 children and invite them to a meeting at the schools. At these meetings we will provide parents with information about the podcast trial and seek their consent to participate.

Because parents who attend meetings might be different than those who do not, we will also make an effort to reach parents who will not have attended the meetings through phone calls, where possible.

Parents who accept to participate will be asked to sign a Consent Form (Additional files 1 and 2) before randomisation to begin their participation in the study.

We will provide information about the trial to participants in a brochure designed as part of a package inviting parents to participate. This information will also be available on the participants’ Informed Consent Forms and will be written in the two most commonly spoken languages (English and Luganda).

### Random allocation

#### Methods for stratification and randomisation

We will stratify our sample proportionately by the highest level of education attained (primary school and below, secondary school, or tertiary education) and whether their children are in a school that is in the intervention or control arm of the IHC primary school resources trial.

We will use computer-generated blocked randomisation. A statistician or other senior researcher at the clinical trials unit at the College of Health Sciences, Makerere University who is not a member of the IHC research team will generate the allocation sequences for the two comparison groups. A web-based random number generator at www.sealedenvelope.com will be used to obtain random permuted blocks with varying block sizes of 4 and 6, and equal allocation ratios, both within blocks and within strata, as shown in Table 1 below.

**Table 1 Tab1:** Excerpt from a sample randomisation list^a^

Column 1	2	3	4	5	6	7
Block identifier	Block size	Sequence within block	Allocation group	Education stratum	Number within stratum	Study code
1	4	1	Group A	≤ primary	1	YL9
1	4	2	Group A	≤ primary	2	PX5
1	4	3	Group B	≤ primary	3	JP3
1	4	4	Group B	≤ primary	4	OB2
2	4	1	Group A	≤ primary	5	XD6
2	4	2	Group A	≤ primary	6	JD0
2	4	3	Group B	≤ primary	7	NU5
2	4	4	Group B	≤ primary	8	SS0
3	4	1	Group B	≤ primary	9	SK0
3	4	2	Group A	≤ primary	10	QN4

^a^List generated from www.sealedenvelope.com

As shown in Table 1 above, the list will have study codes that are unique for each participant (column 7), against which we will attach an ordered array of numbers (column 6) spanning the full breadth of our sample size within each stratum. Each study code will be printed on a separate opaque envelope.

#### Methods for allocation concealment

The allocation group corresponding to each study code will be printed on a separate slip, inserted and sealed in the corresponding opaque envelope. As shown in the list above, the first participant to be recruited among those with primary or no education will have the study code YL9 on their envelope, inside of which will be a small note with their allocation group (group A).

To reduce the risk of bias during allocation a separate list containing the study participant number, and corresponding study code and number within each stratum, will be generated for each of the three education-level strata (up to and including primary, at least secondary and tertiary), as shown in Table 2 below. This list – which will not identify the study arm – will be given by the statistician to a research assistant who will be in charge of group allocation.

**Table 2 Tab2:** Sample participant recruitment lists for each stratum

Stratum 1: Primary school and below		Stratum 2: At least secondary school		Stratum 3: At least tertiary education	
Number within stratum	Study code	Number within stratum	Study code	Number within stratum	Study code
1	YL9	1	FO4	1	TH4
2	PX5	2	HG6	2	UW0
3	JP3	3	GS3	3	AT5
4	OB2	4	PS9	4	SX4
5	XD6	5	YE9	5	UJ7
6	JD0	6	BH7	6	XD9
7	NU5	7	HN6	7	RJ7
8	SS0	8	TY7	8	CS1
9	SK0	9	DT3	9	BC4
10	QN4	10	FZ1	10	ED1

Upon completion of procedures for confirming consent of a willing participant the research assistant responsible for recruiting the participant will call the research assistant in charge of group allocation. The research assistant responsible for allocation will then open the next available envelope in the stratum, corresponding to the participant’s education level and study arm of the child’s school, to determine the study group to which the parent will be allocated.

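### Stratification is declared by education and school arm (six strata), but the lists described cover three education strata only, and the analysis model names education alone

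*Protocol article*

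**What the plan says.** All places are in the Protocol article.

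**Two factors, six strata**
- *Methods for stratification and randomisation* gives the first factor in these words: "We will stratify our sample proportionately by the highest level of education attained (primary school and below, secondary school, or tertiary education"). The second factor is "whether their children are in a school that is in the intervention or control arm of the IHC primary school resources trial". The same section promises "equal allocation ratios, both within blocks and within strata", using "random permuted blocks with varying block sizes of 4 and 6".
- *Methods for allocation concealment*, closing sentence: the allocating research assistant "will then open the next available envelope in the stratum, corresponding to the participant’s education level and study arm of the child’s school".

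**One factor, three strata**
- *Methods for allocation concealment*, list sentence: a separate list "will be generated for each of the three education-level strata (up to and including primary, at least secondary and tertiary").
- Same section, worked example: "the first participant to be recruited among those with primary or no education will have the study code YL9 on their envelope".
- Table 1 has one stratum column, for education, and numbers participants within it. Table 2 sets out three recruitment lists, one per education level.
- *Analysis*: the models carry a single stratification variable, identified in brackets as education.

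*Subgroup and exploratory analyses* plans an interaction test between the podcast and the school teaching resources. *Trial status* says that participants are being recruited.

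**The concern.** The design statement and the envelope rule need a separate randomisation sequence for each combination of education level and school arm. The lists that would carry this out are described by education only. A research assistant holding three education lists has no series that corresponds to school arm, so the closing instruction cannot be followed as written.

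Three things are at stake:
- **Reporting.** The trial report must state the stratification that was used, and the protocol supports two different statements.
- **Balance.** If three lists are in use, each permuted block can mix parents from both school arms, so podcast and control numbers within a school arm are left partly to chance. The trial itself treats school arm as a factor of interest.
- **Analysis.** The models should carry the factors used in the randomisation. The Analysis section lists one of the two declared.

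**Working it through.** The plan gives no figure to reproduce here. The check is a count, followed by the size of the consequence.

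**1. Count of strata.** Declared: 3 education levels × 2 school arms = 6. Lists described: 3.

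**2. Can three lists serve six strata?** The example gives code YL9 to the first recruit with primary or no education, whichever arm the child's school is in. With six strata there would be two such first recruits, one per school arm, each at the head of a separate series. The example is therefore a three-stratum procedure. It agrees with the list sentence and conflicts with the closing sentence of the same section.

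**3. Imbalance by school arm with three lists.**
- Inputs: 497 participants (*Sample size*), 1:1 allocation, so 248.5 per podcast group. About half of the selected schools come from each school arm (*Sampling technique*). Assumption: half of the parents do too, and they arrive in random order.
- SD of the difference between podcast groups in the share of intervention-school parents: √[0.25 × (1/248.5 + 1/248.5)] = 0.0449, or 4.5 percentage points.
- 95% range: 1.96 × 0.0449 = 0.088, or ±8.8 points.
- In participants within one school arm: 0.0449 × 248.5 ≈ 11 (SD), and 1.96 × 11.16 ≈ 22.

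**4. Simulation with blocks of 4 and 6** (3,000 runs, equal thirds by education assumed). Absolute podcast-minus-control difference in numbers within one school arm:

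| Lists | Mean | 95th percentile |
|---|---|---|
| 3 (education) | about 9 | 22 |
| 6 (education × school arm) | about 1.4 | 3 |

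With six lists the hard limit is 3 per stratum (half of a block of 6), hence 3 × 3 = 9 within a school arm.

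**5. Arrival order.** Parents are recruited at school meetings, and all parents at one school share a school arm. With 30 schools, 15 per arm, and three education lists, simulation gives an SD of about 4.4 points with random arrival and about 2.8 points if schools enrol one after another. The protocol does not state the order, so the SD lies between roughly 2.8 and 4.5 points.

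**6. Effect on the interaction test.** Take equal margins and a difference d in the share from intervention schools. The four cells then hold N(1 ± d)/4 participants, and the variance of the interaction estimate in an equal-variance linear model is proportional to (16/N) × 1/(1 − d²). At d = 0.088 the inflation is 1/(1 − 0.0077) = 1.008, or 0.8%.

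**The case against.** The strongest reply is that school arm is provided for. It is declared as a factor, equal allocation is promised within strata, and the closing sentence has the assistant choose the envelope "corresponding to the participant’s education level and study arm of the child’s school, to determine the study group to which the parent will be allocated". Table 1 is labelled an excerpt from a sample list and Table 2 a set of sample lists. Both show format, and a missing school-arm column does not prove how the real lists are built. On this view the list sentence is loose wording.

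Part of this stands. A reader might infer that stratification by school arm is not being carried out. The document does not support that, because one of its own instructions says that it is. The tables alone would not establish the mismatch either. But the reply does not dispose of the list sentence, the worked example or the Analysis section. These are running text, not illustrations, and all three rest on education alone.

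Two further inferences are tempting and also fail:
- *Concealment would be broken.* Nothing describes an assistant improvising two queues from one series. Even then the envelopes are sealed and opaque, and the list handed over does not show the study arm. Incomplete blocks would be the realistic consequence.
- *The podcast-by-school-resources analysis depends on exact balance.* It does not. A model containing school arm and the interaction is valid under chance imbalance, and the loss of precision is about 0.8% at the 95% extreme.

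**Conclusion.** The protocol contradicts itself on its stratification factors. The declaration and the envelope rule use two (six strata). The list sentence, the worked example, the sample tables and the analysis model use one (three strata). The lists as described cannot deliver equal allocation within education-by-school-arm strata. Which procedure is actually running cannot be determined from the document.

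The consequence is moderate. Overall balance and balance by education hold under either reading, and the main comparison is validly randomised. If three lists are in use, the cost is a misstated design and chance imbalance by school arm, with an SD of up to about 4.5 percentage points. That figure assumes 497 participants, an even split of parents by school arm and random arrival; sequential enrolment by school brings it to about 2.8. The mismatch of six strata with three lists rests on no assumption.

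**What to change.** 1. Establish which lists and envelopes are in use. This comes first, because recruitment has started.
2. If there are six series, correct the list sentence and the worked example to six strata, add a school-arm column to Table 1 and expand Table 2.
3. If there are three, correct the stratification statement and the envelope rule to say that randomisation is stratified by education only. Moving to six lists for the remaining participants is optional. If it is done, record the date and the number already randomised.
4. In either case, include school arm beside education as a fixed effect in the models of the Analysis section.

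Steps 1, 2 and 4, or 1, 3 and 4 without the switch, cost one enquiry to the statistician holding the lists, a text correction and one extra model term. A switch during recruitment would cost more: new sequences, new envelopes and a documented change of procedure.

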### The interventions

Participants in the intervention group will listen to a series of podcast episodes designed to teach people to assess claims made about treatment effects (the IHC podcast). Each episode includes a short story with an example of a treatment claim, a simple explanation of a concept used to assess that claim, another example of a claim illustrating the same concept, and its corresponding explanation. In each story there is a question about the trustworthiness of a claim, which is resolved by applying the relevant key concept. All episodes have a conclusion with a take-home message emphasising the concept of evidence-informed, health decision-making. The examples used in the podcast are for claims made about treatments for health conditions, which are of interest to the target audience, such as malaria, diarrhoea, and HIV/AIDS. We have also included claims made about some common practices, such as contraception, which are of interest to our audience.

The topics and claims were identified from scanning recent mass media reports and interviewing parents [32]. There are eight main episodes in the series covering the nine core concepts (Table 3). Each episode lasts about 5 min. One of the episodes (episode 1) covers two closely related key concepts (1.1 and 5.1 in Table 3). Two additional episodes introduce the podcast and summarise the key messages from the first eight episodes, respectively. The podcast also has a song (the IHC theme song), sections of which play at the beginning, in the background and at the end of the episodes. The lyrics of the song were designed to reinforce the messages of the podcast and focus on being careful about claims, and the important questions to ask when we hear claims made about treatment effects. The final structure, content, presentation of the content in each episode, and the series as a whole was informed by an iterative user-centred process of development and user-testing described in another paper [32]. This process involved consultation with various stakeholders, including parents in our target audience, on the appropriate content to be included, and the presentation of this content in each episode, and in the podcast as a whole [32]. The numbering in the first column in the table below relates to numbering of the key concepts in their respective domains, as presented by Austvoll-Dahlgren et al. [31].

**Table 3 Tab3:** The nine concepts^a^ included in the IHC podcast

Concepts	Explanations	Implications
1.1 Treatments may be harmful	People often exaggerate the benefits of treatments and ignore or downplay potential harms. However, few effective treatments are 100% safe	Always consider the possibility that a treatment may have harmful effects
1.2 Personal experiences or anecdotes (stories) are an unreliable basis for assessing the effects of most treatments	People often believe that improvements in a health problem (e.g. recovery from a disease) were due to having received a treatment. Similarly, they might believe that an undesirable health outcome was due to having received a treatment. However, the fact that an individual got better after receiving a treatment does not mean that the treatment caused the improvement, or that others receiving the same treatment will also improve. The improvement (or undesirable health outcome) might have occurred even without treatment	Claims made about the effects of a treatment may be misleading if they are based on stories about how a treatment helped individual people, or if those stories attribute improvements to treatments that have not been assessed in systematic reviews of fair comparisons
1.3 A treatment outcome may be associated with a treatment, but not caused by the treatment	The fact that a treatment outcome (i.e. a potential benefit or harm) is associated with a treatment does not mean that the treatment caused the outcome. For example, people who seek and receive a treatment may be healthier and have better living conditions than those who do not seek and receive the treatment. Therefore, people receiving the treatment might appear to benefit from the treatment, but the difference in outcomes could be because of their being healthier and having better living conditions, rather than because of the treatment	Unless other reasons for an association between an outcome and a treatment have been ruled out by a fair comparison, do not assume that the outcome was caused by the treatment
1.4 Widely used treatments or treatments that have been used for a long time are not necessarily beneficial or safe	Treatments that have not been properly evaluated but are widely used or have been used for a long time are often assumed to work. Sometimes, however, they may be unsafe or of doubtful benefit	Do not assume that treatments are beneficial or safe simply because they are widely used or have been used for a long time, unless this has been shown in systematic reviews of fair comparisons of treatments
1.6 Opinions of experts or authorities do not alone provide a reliable basis for deciding on the benefits and harms of treatments	Physicians, researchers, patient organisations, and other authorities often disagree about the effects of treatments. This may be because their opinions are not always based on systematic reviews of fair comparisons of treatments	Do not rely on the opinions of experts or other authorities about the effects of treatments, unless they clearly base their opinions on the findings of systematic reviews of fair comparisons of treatments
2.1 Evaluating the effects of treatments requires appropriate comparisons	If a treatment is not compared to something else, it is not possible to know what would happen without the treatment, so it is difficult to attribute outcomes to the treatment	Always ask what the comparisons are when considering claims made about the effects of treatments. Claims that are not based on appropriate comparisons are not reliable
2.2 Apart from the treatments being compared, the comparison groups need to be similar (i.e. ‘like needs to be compared with like’)	If people in the treatment comparison groups differ in ways other than the treatments being compared, the apparent effects of the treatments might reflect those differences rather than actual treatment effects. Differences in the characteristics of the people in the comparison groups might result in estimates of treatment effects that appear either larger or smaller than they actually are. A method, such as allocating people to different treatments by assigning them random numbers (the equivalent of flipping a coin), is the best way to ensure that the groups being compared are similar in terms of both measured and unmeasured characteristics	Be cautious about relying on the results of nonrandomised treatment comparisons (for example, if the people being compared chose which treatment they received). Be particularly cautious when you cannot be confident that the characteristics of the comparison groups were similar. If people were not randomly allocated to treatment comparison groups, ask if there were important differences between the groups that might have resulted in the estimates of treatment effects appearing either larger or smaller than they actually are
4.1 The results of single comparisons of treatments can be misleading	A single comparison of treatments rarely provides conclusive evidence and results are often available from other comparisons of the same treatments. These other comparisons may have different results or may help to provide more reliable and precise estimates of the effects of treatments	The results of single comparisons of treatments can be misleading
5.1 Treatments usually have beneficial and harmful effects	Because treatments can have harmful effects as well as beneficial effects, decisions should be informed by the balance between the benefits and harms of treatments. Costs also need to be considered	Always consider the trade-offs between the potential benefits of treatments and the potential harms and costs of treatments

^a^From Austvoll-Dahlgren et al. [31]

A summary of the concepts contained in each episode of the podcast is shown in Table 4 below.

**Table 4 Tab4:** The concepts^a^ contained in each episode of the podcast

Episode	1	2	3	4	5	6	7	8
Concept^a^	1.1 + 5.1	2.1	1.2	1.3	1.4	1.6	2.2	4.1

^a^See Table 3 for the full description of the concepts and their implications

Participants in the control group will receive typical public service announcements about conditions of interest to our target audience, including malaria, HIV/AIDS, and diarrhoea, that have been included in the podcast. These audio messages are already being aired or have in the recent past been aired on radio. They are freely available and will be sourced from radio stations and media houses involved in disseminating information from the Ministry of Health.

